### Primary outcomes

5.1

#### MoCA

5.1.1

MoCA is used to evaluate cognitive functioning, including attention, concentration, executive functioning, memory, expression, visual-structural skills, abstract thinking, computation, and orientation. The total score ranging from 18 to 25 indicates MCI. If the patient with no more than 12 years of education, then add 1 point to the total score.

### Secondary outcomes

5.2

#### MMSE

5.2.1

The Mini-mental state examination (MMSE) could evaluate memory function, and offers a rapid and accurate measure of intellectual status and cognitive deficits. The score adjusted based on education level, with cutoff criteria for normal cognitive functioning are as follows: more than 17 points for uneducated individuals, more than 20 points for low-educated individuals, and more than 24 points for highly educated individuals.

#### ISI

5.2.2

Insomnia Severity Index Scale (ISI) is designed to evaluate insomnia symptoms experienced in the past 2 weeks. It consists of 7 items, comprising daytime function and nighttime symptoms. Each item is scored from 0 to 4. The criteria for insomnia are as follows: mild insomnia ranges from 8 to 14, moderate insomnia ranges from 15 to 21, and severe insomnia ranges from 22 to 28. This assessment tool is invaluable for evaluating the outcomes of interventions targeting insomnia.

#### PHQ-9, GAD-7, and AES-I

5.2.3

Anxiety, depression, and apathy are recognized as risk factors for dementia. Considering of the characteristics of patients, we incline to use more concise, objective, and efficient scales in emotional assessment. The Patient Health Questionnaire-7 (PHQ-9) consists of 9 items, each item rated on 0–3 score. The Generalized Anxiety Disorder (GAD-7) scale comprises 7 items, and each item ratings from 0 to 3 to assess psychogenic anxiety symptoms. The Apathy Evaluation Scale-Informant (AES-I) consists of 18 items, each item rated on a scale of 0–3. It will be used to assess the apathy degree of patients. Higher scores indicate more severe symptoms of depression, anxiety, or apathy.

#### SF-12

5.2.4

The Short Form 12 Health Survey (SF-12) scale includes 8 dimensions of 12 items. This scale is widely used in large-scale health measurement. The score is positively correlated with the level of health quality.

### fNIRs data of brain function

5.3

The fNIRS data will be recorded using the NIRx Imager system (NIRx Medical Technologies, Germany). Fifteen transmitters and fifteen detectors will be utilized to capture cerebral oxygenation signals. Initial scalp localization will be performed using established stereospecific and anatomical markers. The positions of the emitters, detectors, and the 43 channels covering the frontal and temporal lobes will be precisely identified (Figure 5). To capture the fNIRS data, the device will emit near-infrared light at wavelengths of 785 nm and 830 nm, with a continuous wave frequency of 3.096 Hz. Before the testing procedure, participants will be briefed on the study objectives and instructed to maintain optimal stillness of their heads throughout the testing process to minimize potential errors. The study procedure includes two parts: a resting test and an N-back working memory test.

**Figure 5 fig5:**
[figure not shown]
The positions of the emitters, detectors, and the 43 channels.

During resting test, all anticipants will be required to remain seated with their eyes closed for 300 s. In the N-back working memory task, a block design alternating between 0-back and 2-back numerical tasks will be employed. In the 0-back task, 12 numbers will be presented randomly, and participants will be asked to identify whether the displayed number is “9” from a range of 0–9. In the 2-back task, participants will be required to determine whether the current number matches the one shown two positions earlier. The task sequence will follow a “0-2-0-2” pattern, with six blocks for each task type, and a 20 s interval marked by a “+” sign on the screen (Figure 6). The correct rate for the 0-back and 2-back tasks will be calculated to the total number of each task type.

**Figure 6 fig6:**
[figure not shown]
Resting test and working memory test processes.

## Assessment of safety and “deqi” sensations

6

Vital signs including heart rate, blood pressure, respiration rate, and oxygen saturation will be monitored prior and following each intervention. Any adverse effects (AEs) will be recorded by the operator, with immediate symptomatic treatment and subsequent analysis for causation. Severe AEs will be immediately documented and reported to the Ethics Committee of the Affiliated Hospital of Chengdu University of Traditional Chinese Medicine within 24 h.

We will use an acupuncture sensation scale to assess “deqi” sensations, including soreness, numbness, heaviness, fullness, pain, and anxiety. Participants will also be able to describe any additional sensations they experience. Each sensation will be rated on a 0–10 scale, where 0 indicates no sensation and 10 represents the most intense sensation. Participants will complete this scale after each session, which will facilitate systematic collection and analysis of “deqi” sensations.

## Data analysis

7

Data analysis will follow the intention-to-treat (ITT) strategy and will be conducted using IBM SPSS version 26.0 software (IBM Corp, New York). A *p*-value of ≤0.05 will be considered statistically significant. To address missing data, the Last Observation Carried Forward (LOCF) method will be employed for imputation. Continuous variables will be expressed as mean ± standard deviation, while categorical variables will be presented as numbers and percentages. Categorical variables will be analyzed using the Chi-Square Test. For continuous variables that follow a normal distribution, comparisons between groups will be made using an independent samples *t*-test, while paired samples *t*-tests will be used for pre- and post-treatment comparisons within the same group. For continuous data that do not follow a normal distribution, the Mann–Whitney U test will be used, with results expressed as the median and interquartile range. *p*-values obtained from the statistical tests, both for clinical outcomes and fNIRS data, will be corrected using the false discovery rate (FDR) method to account for multiple comparisons.

The raw fNIRS data will be preprocessed using NIRSPARK software, which includes format conversion, motion correction, artifact processing, and bandpass filtering. Data analysis will be performed using a dedicated module in MATLAB (R2020a).

Previous studies have demonstrated that patients with cognitive impairment due to insomnia exhibit working memory deficits correlated with cognitive performance, alongside altered connectivity patterns between the prefrontal and temporal regions (28). These findings suggest that these regions may constitute the neural basis of cognitive impairment in this population. Furthermore, acupuncture has been shown to modulate network connectivity within the prefrontal and temporal lobes in insomnia patients (29). Therefore, in this study, we will select the prefrontal and temporal regions as the regions of interest (ROIs) for activation and functional connectivity analyses. Visual representations will be generated to facilitate intuitive presentation.

In MATLAB, the NIRS-SPM will be used for analysis, converting raw data into “.mat” format. The modified Beer–Lambert law will be applied to calculate blood oxygen concentration from the raw optical intensity data. The Topo-maker module will determine the optode configuration based on standard three-dimensional brain space positional information. Initial data checks will identify channels with potential abnormalities or noticeable noise, labeling them as bad channels.

To address physiological noise and head motion artifacts, temporal derivative distribution repair (TDDR) will be employed to remove spike artifacts and baseline shifts. Subsequently, a band-pass filter will be applied to eliminate noise from heartbeats, respiration, and Mayer waves, setting the filter range to 0.01–0.1 Hz according to the experimental paradigm.

For functional connectivity analysis, the data will be segmented into resting-state and task-state periods (0-back, 2-back). Connectivity measures, including correlation coefficients (corr), coherence (coh), and phase-locking values (PLV), will be calculated across all channels for each subject. Individual connectivity matrices will be constructed, and group-level averages will be computed for each condition. Statistical analyses, such as *t*-tests or ANOVA, will compare differences between conditions. The results will be visualized using connectivity matrices and brain network plots, and the findings will be interpreted in relation to cognitive function and task-related changes.

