**Methods and design:**

This study is a single-center randomized controlled trial. Participants will be randomly assigned to the manual acupuncture group or the placebo acupuncture group for an 8-week intervention period. fNIRS data will be collected during resting test and working memory test at baseline and at end of the intervention. The primary outcome is the change of the Montreal Cognitive Assessment (MoCA) score, secondary outcomes include the change of Mini-Mental State Examination (MMSE), Insomnia Severity Index (ISI), Patient Health Questionnaire-9 (PHQ-9), Generalized Anxiety Disorder Scale (GAD-7), and Apathy Evaluation Scale-Informant (AES-I).

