### Sample size calculation

3.3

According to a prior clinical study (32), sample size estimation is based on the Montreal Cognitive Assessment (MoCA) score. The differences in MoCA scores before and after treatment was (3.22 ± 1.88) for the acupuncture group and (1.97 ± 1.77) for the placebo acupuncture group. In the formula, with *α* = 0.05, *β* = 0.10, and k = 1, a sample size of 37 cases per group was calculated. Considering a dropout rate of 20%, we determined a sample size of 45 cases per group. Consequently, the total number of cases in both groups will be 90.

Using brain imaging data as an indicator of acupuncture-related studies, the sample typically ranged from 10 to 25 individuals per group (33–35). Thus, we will enroll at least 20 participants per group in fNIRS scanning. Considering a dropout rate of 20%, we determined a sample size of 24 cases per group.
$$n=\frac{{\left(u_{\alpha }+\mu_{\beta }\right)}^{2}\left(1+1∕k\right)\sigma^{2}}{\delta^{2}}$$

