## Outcome measures

5

Each participant will be evaluated by a medical professional blinded to the group assignment and intervention. Assessments will occur at five time points: baseline, 4 weeks, 8 weeks, 12 weeks, and 20 weeks. The schedule of this study is listed in Table 3.

**Table 3 tab3:** Study schedule.

Timepoint	Enrolment	Baseline	Treatment phase		Follow-up phase	
	1 week	0 week	4 weeks	8 weeks	1 month	3 months
Enrolment						
Eligibility screen	**×**					
Medical history	**×**					
Informed consent		**×**				
Allocation		**×**				
Interventions						
Manual acupuncture		**×**	**×**	**×**		
Placebo acupuncture		**×**	**×**	**×**		
Health education		**×**	**×**	**×**		
Assessments						
Demographics	**×**					
fNIRS scanning		**×**		**×**		
PSQI	**×**	**×**				
MoCA	**×**	**×**	**×**	**×**	**×**	**×**
ISI		**×**	**×**	**×**	**×**	**×**
MMSE		**×**	**×**	**×**	**×**	**×**
PHQ-7		**×**	**×**	**×**	**×**	**×**
GAD		**×**	**×**	**×**	**×**	**×**
AES		**×**	**×**	**×**	**×**	**×**
SF-12		**×**	**×**	**×**	**×**	**×**
Safety assessment		**×**	**×**	**×**		
Vital sign		**×**	**×**	**×**		
Use of sleep medications		**×**	**×**	**×**	**×**	**×**

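### LOCF as the stated primary missing-data method scores patients lost before week 4 as zero MoCA change: it shrinks the planned difference under equal dropout and creates a false one if dropout differs by arm

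*Protocol article*

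**What the plan says.** In Data analysis (section 7) the article fixes both the analysis set and the imputation: "Data analysis will follow the intention-to-treat (ITT) strategy", and "To address missing data, the Last Observation Carried Forward (LOCF) method will be employed for imputation". The completed data then go into a simple two-group test: for normally distributed variables, "comparisons between groups will be made using an independent samples *t*-test". No other missing-data method is named.

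The endpoint is given in the abstract: "The primary outcome is the change of the Montreal Cognitive Assessment (MoCA) score". Outcome measures (section 5) sets the visits: "Assessments will occur at five time points: baseline, 4 weeks, 8 weeks, 12 weeks, and 20 weeks". Table 3 lists MoCA at screening and at each of these visits, so nothing is measured between baseline and week 4.

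Sample size calculation (3.3) assumes mean changes of 3.22 (SD 1.88) with acupuncture and 1.97 (SD 1.77) with placebo. It then allows for losses: "Considering a dropout rate of 20%, we determined a sample size of 45 cases per group". The 20% is not split by arm or by time.

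**The concern.** LOCF assumes that a patient's score stops moving when the patient leaves. The plan's own figures say otherwise: both arms, placebo included, are expected to improve well above zero. Carrying a baseline score forward therefore gives a value that contradicts the planning model, and carrying a week-4 score gives a partial one.

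Two consequences follow. With similar dropout in both arms, the estimated difference is pulled toward zero and power can be lost. With unequal dropout, the arm that loses more patients is scored lower even if the treatments do not differ, so a false effect can appear in either direction.

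At follow-up, a patient who was seen on treatment but is lost by week 12 has the last on-treatment score copied to weeks 12 and 20, as if the benefit had been maintained.

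The sample size also treats dropouts as lost (37 raised by 20%), whereas ITT with LOCF keeps them in with these values.

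**Working it through.** **Inputs.** Changes 3.22 (SD 1.88) and 1.97 (SD 1.77), α = 0.05, β = 0.10, 20% dropout and 45 per arm, all from section 3.3. Week 8 is taken as the primary time point, since section 3.3 uses the change from before to after treatment.

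**The plan's own figure.** Pooled SD = √[(1.88² + 1.77²)/2] = 1.826; δ = 3.22 − 1.97 = 1.25. Then n = 2(1.645 + 1.282)² × 1.826²/1.25² = 36.5, so 37 per arm, and 37 × 1.2 = 44.4, so 45. The stated figures reproduce, but 37 needs a one-sided α; a two-sided 5% gives 44.8, so 45 before dropout. Power below is two-sided unless noted.

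**LOCF mean.** Let p be the proportion lost and f the fraction of the gain carried (0 if lost before week 4; 0.5 assumed if lost after). If loss is unrelated to outcome, the arm mean becomes μ[1 − p(1 − f)].

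**Equal 20% dropout, planned effect present.**
- All lost before week 4: means 0.8 × 3.22 = 2.576 and 0.8 × 1.97 = 1.576, difference 1.00. The variance is (1 − p)(SD² + μ²) − [(1 − p)μ]², which is 4.486 and 3.127, so the SD rises to 1.951. SE = 1.951 × √(2/45) = 0.411. Power = Φ(1.00/0.411 − 1.96) = 0.68; simulated 67%. One-sided: 0.78.
- Half lost early, half late: difference 1.25 × 0.85 = 1.06. Simulated power 73% (week-4 SD equal to week-8 SD).
- All lost after week 4: difference 1.25 × 0.9 = 1.125. Power about 80% if the week-4 SD equals the week-8 SD, about 85% if it is half.
- Observed cases, 36 per arm: SE = 1.826 × √(2/36) = 0.430, power = Φ(1.25/0.430 − 1.96) = 0.83; simulations give about 80–82%. One-sided: 0.90.
- Type I error under LOCF with no true effect: simulated at about 5%.

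**Unequal dropout, no true effect, both arms gaining 1.97.** The false difference is 1.97 × (1 − f) × (p placebo − p acupuncture).

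| Dropout, acupuncture v placebo | Timing | False difference | Two-sided false-positive rate |
|---|---|---|---|
| 10% v 30% | all before week 4 | 1.97 × 0.20 = 0.39 | 18% |
| 10% v 30% | half early, half late | 1.97 × 0.75 × 0.20 = 0.30 | 12% |
| 10% v 30% | all after week 4 | 1.97 × 0.5 × 0.20 = 0.20 | 8–9% |
| 15% v 25% | all before week 4 | 1.97 × 0.10 = 0.20 | 8% |

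Reversing the imbalance reverses the sign (30% v 10%, all early: −0.39). Observed cases under the null, 40 v 32 patients: 5%.

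**Unequal early dropout, planned effect present.** 10% v 30% gives 0.9 × 3.22 − 0.7 × 1.97 = 1.52; 30% v 10% gives 0.7 × 3.22 − 0.9 × 1.97 = 0.48, against a true 1.25.

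**The case against.** The strongest reply is that the extreme figures need assumptions the article does not make. It gives 20% dropout overall and says nothing of timing or arm. The 67% power requires every loss to fall before week 4, and the 18% false-positive rate also requires a threefold imbalance. If all losses come after week 4, LOCF has about the same power as observed cases or slightly more. Several design features work against unequal loss: the same device in both arms, blinded participants, exclusion of people unlikely to finish, and free acupuncture for controls afterwards. All of this stands, so the results are given as ranges. It does not rule out imbalance over 24 sessions of penetrating versus non-penetrating needling.

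Four stronger readings are tempting, and the documents do not support them:
- A reader might infer that the primary estimate is biased toward acupuncture, or that type I error is uncontrolled in general. With equal dropout the estimate is attenuated and the error rate stays near 5%; only unequal loss creates a false effect.
- A reader might infer that the standard errors are seriously wrong because imputed values count as observed. The near-nominal error rate under equal dropout gives no sign of that.
- A reader might infer that weeks 12 and 20 always carry an on-treatment score. A patient seen at week 12 and missing at week 20 carries an off-treatment score.
- A reader might fault the absence of sensitivity analyses. Those could sit in an analysis plan that is not shown; the point here is the choice of LOCF itself.

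The rates also use unadjusted p-values, whereas the article plans FDR correction. The usual step-up correction never lowers a p-value, so power and false-positive rates under the full rule would be no higher than shown. The displaced estimate is unaffected. Finally, the article calls the study exploratory, which lessens the consequence but does not remove the error.

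**Conclusion.** The point holds as a conditional one. Following the article as written gives patients lost before week 4 a zero change that conflicts with its own expected gains, and this enters the primary comparison.

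Under equal 20% dropout the cost is a difference of 1.00 to about 1.12 instead of 1.25, and power from 67% to about 80–85%, against about 80–82% for observed cases. Under an assumed 10% v 30% imbalance it is a false difference of about 0.2 to 0.4 points and a false-positive rate of about 8% to 18%. LOCF therefore cannot be defended as reliably conservative.

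These figures rest on dropout unrelated to outcome, normally distributed changes, half the gain reached by week 4, a week-4 to week-8 correlation of 0.5 where timing is mixed or late, and no FDR correction. The dropout timing and the split by arm are assumptions; neither is in the article.

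**What to change.** In Data analysis, replace LOCF for the primary analysis and the follow-up visits with a mixed model for repeated measures on the observed MoCA scores: arm, visit, arm by visit and baseline MoCA, with the week-8 contrast as primary.

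Patients lost before week 4 need an explicit rule. If baseline MoCA is only a covariate, they have no outcome record and drop out of the model, so it could not be described as using all randomised patients. Either enter baseline MoCA in the outcome vector with a common baseline mean across arms, or use multiple imputation; otherwise state that these patients do not contribute.

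LOCF may stay as a sensitivity analysis. The new primary analysis relies on data being missing at random, which a delta-adjusted or reference-based sensitivity analysis can check.

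The cost is a change of wording: MoCA is already scheduled at every visit, no patients or visits are added, and the named software can fit the model. The article's section 8 gives a route for such changes through ethics approval. It should be settled before dropout by arm is known.

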### Randomization and blinding

3.10

Participants will be randomly assigned to two groups in a 1:1 ratio using computer-generated random numbers. During intervention phase, participants will be administered separately in quiet treatment rooms to prevent interactions from different groups. Throughout the study, researchers, acupuncturist, efficacy assessors, and data statisticians will remain segregated. Only the acupuncturist aware of the group assignment result. Participants, evaluators, and analysts will be blinded to group assignments.

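### The between-group test of MoCA change does not adjust for baseline and may switch to a rank test; a prespecified ANCOVA would usually be more precise and would keep the mean difference as the effect measure.

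*Protocol article*

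**What the plan says.** The abstract defines the endpoint: "The primary outcome is the change of the Montreal Cognitive Assessment (MoCA) score". The study schedule (Table 3) has MoCA and every secondary scale measured at baseline, during treatment and at follow-up.

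Section 7 (Data analysis) sets one rule for all continuous outcomes. It reads "For continuous variables that follow a normal distribution, comparisons between groups will be made using an independent samples" t-test, and then "For continuous data that do not follow a normal distribution, the Mann–Whitney U test will be used", with the results of the rank test given as median and interquartile range. Baseline values appear in section 7 only through within-group paired t-tests. No ANCOVA, covariate or repeated-measures model is named for the clinical scales. Section 7 also specifies intention-to-treat analysis with last observation carried forward (LOCF).

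The sample size (section 3.3) rests on mean changes: "The differences in MoCA scores before and after treatment was (3.22 ± 1.88) for the acupuncture group and (1.97 ± 1.77) for the placebo acupuncture group". The remaining inputs are "with *α* = 0.05, *β* = 0.10, and k = 1", leading to "a sample size of 37 cases per group was calculated" and then "Considering a dropout rate of 20%, we determined a sample size of 45 cases per group". Section 3.10 describes allocation as "randomly assigned to two groups in a 1:1 ratio using computer-generated random numbers" and names no stratification by baseline cognition.

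**The concern.** Two features of section 7 deserve attention.

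**Precision.** A change score fixes the coefficient on baseline at 1. ANCOVA estimates that coefficient from the data, so its residual variance cannot be larger, apart from one degree of freedom. When r is below 1 and the two variances are equal, subtraction over-corrects for baseline: a chance baseline difference between arms shifts the expected difference in change by (1 − r) times that difference, in the opposite direction. Randomisation makes this zero on average, but it adds noise in a trial of 45 per arm without stratification.

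**Effect measure.** Whether the primary result is a comparison of means or of ranks depends on how the observed data look. On the rank branch, the reported summary is no longer the mean difference on which the trial was sized.

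At stake is the precision of the main result in a trial with little power to spare, and a primary effect measure that is not settled before the data are seen.

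**Working it through.** **Inputs from section 3.3.** Difference 3.22 − 1.97 = 1.25 points. Pooled SD of change √[(1.88² + 1.77²)/2] = 1.826. β = 0.10, k = 1. The sidedness of α = 0.05 is not stated.

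**Reproducing the plan's figure.** n = (u_α + u_β)² × 2 × 1.826² / 1.25².
- One-sided α (1.645 + 1.282): n = 36.5, rounded up to 37. This matches.
- Two-sided α (1.960 + 1.282): n = 44.8, rounded up to 45. This does not match 37.
- Dropout: 37 × 1.2 = 44.4, rounded up to 45. This matches. Dividing instead, 37/0.8 = 46.25, would give 47.

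The stated 37 therefore implies a one-sided α. If 20% of 45 drop out, 36 per arm complete.

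**Variance of the two analyses.** Let s0 and s1 be the baseline and week-8 SDs and r their correlation.
- Change score: s0² + s1² − 2·r·s0·s1.
- ANCOVA: s1²(1 − r²).
- Saving (the difference between them): (s0 − r·s1)², never negative.
- With s0 = s1, the ratio of ANCOVA to change score is (1 − r²)/[2(1 − r)] = (1 + r)/2.

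**Power.** Two-sided α = 0.05, noncentral t, difference 1.25, SD = 1.826 × √[(1 + r)/2] for ANCOVA. The protocol does not give r, so the range is an assumption.

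| Analysis | Variance ratio | 36 per arm | 45 per arm |
|---|---|---|---|
| t-test on change | 1 | 81.7% | 89.5% |
| ANCOVA, r = 0.5 | 0.75 | 91.1% | 96.0% |
| ANCOVA, r = 0.6 | 0.80 | 89.3% | 94.9% |
| ANCOVA, r = 0.7 | 0.85 | 87.4% | 93.6% |
| ANCOVA, r = 0.8 | 0.90 | 85.5% | 92.3% |

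The 36 column is completers only. The 45 column keeps everyone, as ITT with LOCF would, and ignores any dilution from carried-forward values. With 36 per arm, ANCOVA reaches 90% only for r up to about 0.55.

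**Sensitivity to unequal spread.** Take s0 = 0.7·s1 (assumed). The variance ratio is then (1 − r²)/(1.49 − 1.4r):
- r = 0.6: 0.64/0.65 = 0.985, a saving of 1.5%.
- r = 0.7: 0.51/0.51 = 1.00, no saving.
- r = 0.8: 0.36/0.37 = 0.973, a saving of about 3%.

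**The rank branch.** If the data were in fact normal, Mann–Whitney has relative efficiency of about 0.955. By normal approximation, power with 36 per arm is about 81%, against 83% for the t-test on the same approximation. The power loss is small; the main cost is the change of effect measure.

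**The case against.** The strongest reply is that nothing here is an error. In a 1:1 randomised trial, a t-test on change is unbiased and matches the basis of the sample size. That stands: this is a point about efficiency and prespecification, not validity.

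A reader might infer from the missing covariate that the plan ignores baseline MoCA. The documents do not support that. The abstract makes change the outcome and section 3.3 sizes the trial on before–after differences, so baseline is used by subtraction. The comparison is between two ways of using it.

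A reader might also take 82% as the power of the planned analysis. That figure counts completers only. Under ITT with LOCF up to 45 per arm could be analysed, and unadjusted two-sided power is then 89.5% before any dilution. This stands, so both sets of figures are needed.

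The size of the gain depends on an r that is not given and on equal variances. Section 5.1.1 gives 18 to 25 as the MoCA range for MCI, and Table 3 lists MoCA at enrolment, so a compressed baseline spread is plausible. In that case the gain may nearly vanish. This also stands.

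Finally, the article states the rule for choosing the test in advance, and an unseen SAP may say how normality is judged or add a mean difference. It therefore cannot be said that the 1.25-point difference will never be estimated. What remains is that the stated rule lets the data choose the primary effect measure.

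**Conclusion.** The point holds as a recommended improvement. Section 7 fixes an unadjusted comparison, although a baseline value of every clinical scale will be available. ANCOVA would be at least as precise, apart from one degree of freedom, and would give one effect measure on the scale used to size the trial.

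Under equal variances and r between 0.5 and 0.8, both assumed, the gain is about 4 to 9 percentage points of power with 36 per arm and about 3 to 6 with 45. It is smaller, possibly nil, if baseline scores are less spread out than week-8 scores.

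It would be tempting to conclude that ANCOVA recovers the stated 90% power. That is not established. With 36 completers it does so only for r up to about 0.55 under equal variances. The shortfall comes mainly from the one-sided α implicit in 37 per group, with the dropout inflation adding a little; neither is a fault of the t-test.

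**What to change.** In section 7, name as the primary analysis an ANCOVA of week-8 MoCA on arm and baseline MoCA, or an equivalent repeated-measures model. Report the adjusted mean difference with its 95% CI whatever the normality result. (Week 8 is taken as the primary time point because it ends the intervention; the text should say so.) Use the same model for each secondary scale with its own baseline as covariate. Keep rank-based or bootstrap methods as sensitivity checks.

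The sidedness of α should also be stated, since the covariate cannot be relied on to make up that part of the power.

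The cost is a wording change, made before unblinding and through the amendment route in section 8. No new data or patients are needed.

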Acupuncture, a widely used external therapy, offers advantages over pharmacological treatments, such as avoiding drug toxicity and side effects (48). The efficacy of acupuncture can be explained through various mechanisms, including modulating neurotransmitter release, reducing brain tissue inflammation, eliminating free radicals, inhibiting neuronal apoptosis, and suppressing tau protein expression. Recent studies have assessed the effectiveness of acupuncture (49, 50). Nevertheless, there is a debatable viewpoint suggesting that the efficacy of acupuncture may be primarily attributed to a placebo effect (51). In this study, the effectiveness of acupuncture will be assessed using placebo control to mitigate the non-specific effects of acupuncture. Concurrently, fNIRS will be utilize to investigate the functional characteristics of brain regions in patients, identify imaging characteristics associated with the disease. Compare characteristics before and after the intervention to explore the effect of acupuncture on modulating the function of these regions.

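### For fNIRS, no between-arm contrast is named as the basis for an acupuncture effect; within-arm tests have no descriptive-only role, and the non-normal fallback does not suit paired data

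*Protocol article*

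**What the plan says.** Section 7 (Data analysis) gives the general rules for normally distributed continuous variables in one sentence. First, "comparisons between groups will be made using an independent samples *t*-test". Then come paired t-tests, which "will be used for pre- and post-treatment comparisons within the same group". The threshold is p ≤ 0.05, and neither test is named as the one that decides efficacy. The next sentence gives the only alternative for non-normal data: "For continuous data that do not follow a normal distribution, the Mann–Whitney U test will be used". P-values for clinical outcomes and fNIRS alike "will be corrected using the false discovery rate (FDR) method to account for multiple comparisons".

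The fNIRS-specific text is narrower. The connectivity paragraph of section 7 splits the recordings into rest, 0-back and 2-back periods and says that t-tests or ANOVA "will compare differences between conditions". It names neither arm nor arm by time. Section 9 (Discussion) states the purpose of the repeat scan: "Compare characteristics before and after the intervention to explore the effect of acupuncture on modulating the function of these regions".

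Section 3.5 and Table 3 show that both randomised arms are scanned at baseline and at week 8, with 24 patients per arm.

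**The concern.** Section 2 makes the effect of acupuncture on brain function part of the study's aim. In a randomised placebo-controlled trial, that effect is the difference between arms in what happens from baseline to week 8. A before–after change within the acupuncture arm also contains practice on a repeated N-back task, expectation, regression to the mean, the health education given to both arms and any change in permitted sleep medication. A contrast between 0-back and 2-back describes task load and does not involve treatment. Nor is significance in one arm without significance in the other evidence that the arms differ.

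If the report follows the fNIRS-specific wording, a before–after change could be credited to acupuncture although the placebo scans needed to test that claim will have been collected.

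The non-normal fallback is a separate fault. Mann–Whitney U compares two independent samples. Applied to before and after values from the same patients, it ignores the pairing. Correlation, coherence and phase-locking values are bounded, so non-normality is plausible for these endpoints.

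**Working it through.** **Inputs (section 3.3 unless noted).** MoCA change: acupuncture 3.22, SD 1.88; placebo 1.97, SD 1.77. α = 0.05, β = 0.10, k = 1. Stated size 37 per arm, 45 after dropout. fNIRS: at least 20 per arm, 24 enrolled (also section 3.5). No fNIRS change or SD is given anywhere.

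**Step 1: reproduce the plan's figure.** δ = 3.22 − 1.97 = 1.25. Pooled variance = (1.88² + 1.77²)/2 = 3.334, so SD = 1.826. The stated formula is n = (u_α + u_β)² (1 + 1/k) σ²/δ².
- One-sided α: (1.645 + 1.282)² × 2 × 3.334/1.5625 = 36.5, rounded up to 37. This matches.
- Two-sided α: (1.960 + 1.282)² × 2 × 3.334/1.5625 = 44.8, rounded up to 45. This does not match.

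Sidedness is a separate matter. What counts here is that the trial was sized on a between-arm difference in change.

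**Step 2: the paired test in the placebo arm, MoCA.** Expected t = mean change/(SD/√n). Power comes from the noncentral t with n − 1 df, two-sided 5%.

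| n | SE = 1.77/√n | Expected t | Power |
|---|---|---|---|
| 20 | 0.396 | 4.98 | 99.7% |
| 24 | 0.361 | 5.45 | 99.9% |
| 37 | 0.291 | 6.77 | over 99.99% |

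At n = 37 the expected 95% CI for the placebo change is 1.38 to 2.56. Eleven patients already give 90% power. The rows for 20 and 24 show only how few patients suffice for MoCA; they carry no information about fNIRS.

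**Step 3: the paired test in the acupuncture arm, MoCA.** SE = 1.88/√37 = 0.309, and t = 3.22/0.309 = 10.42. Both arms pass. If acupuncture did exactly what placebo does (1.97 ± 1.77), its arm would still pass with over 99.99% probability at n = 37, by the same arithmetic as step 2. The within-arm result would therefore be the same with or without a specific effect.

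**Step 4: the between-arm test, MoCA.** t = 1.25/(1.826 × √(2/37)) = 2.94, two-sided p about 0.004, power 84% two-sided (normal approximation). This test does separate the arms, and it is much less emphatic than t = 10.42.

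**Step 5: which comparison governs each outcome.**
- *Clinical outcomes:* the between-group t-test in section 7, the sample size in section 3.3 and the placebo rationale in Table 1 (item 6a) all point to the difference between arms.
- *fNIRS:* the section 7 connectivity paragraph compares conditions, and section 9 compares before with after. The general between-group sentence may apply, but no text connects it to the claim that acupuncture modulates these regions.

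**The case against.** The strongest reply is that the between-arm test is already in the plan. It stands first in the sentence that introduces the paired tests. The rules cover continuous variables generally, and the multiplicity sentence mentions fNIRS explicitly, so the tests listed before it can fairly be read to include fNIRS. Section 9 also says that "the effectiveness of acupuncture will be assessed using placebo control to mitigate the non-specific effects of acupuncture", in the same paragraph as the before–after sentence, and a Discussion sentence is not an analysis rule. Scanning both arms twice is the layout for a between-arm comparison.

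Most of this stands. A reader might infer that the acupuncture effect in general is to be judged from before–after tests, or that the placebo arm goes unused. The documents support neither reading. A reader might also carry the MoCA calculation over to fNIRS. That too is unsupported, since no fNIRS variability is given. The protocol states no rule that efficacy means significance in one arm only.

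What the reply does not remove is the ambiguity. Where the text turns to fNIRS, it names two comparisons that do not involve the arms, and it does not say which test decides the mechanistic question. False-discovery-rate correction does not help, because it limits false positives among the hypotheses tested and leaves the within-arm hypothesis as it is.

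On Mann–Whitney, it can be said that the test is meant only as the counterpart of the independent t-test, with the paired counterpart left to a fuller plan. But it is stated immediately after both t-tests as the single alternative for all non-normal continuous data. Taken as written, it is wrong for the paired half.

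**Conclusion.** The concern holds in a limited form. For clinical outcomes the randomised comparison is planned. For fNIRS it may be covered by the general rule but is not made the basis for the mechanistic claim, and the comparisons that are specified cannot support that claim. The paired tests are planned at p ≤ 0.05 with no descriptive-only role. On the protocol's own MoCA figures such a test would be significant in the placebo arm almost surely (t about 6.8 at n = 37), so it cannot separate acupuncture from placebo. The single non-normal fallback does not suit the paired comparisons.

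The calculation assumes that the MoCA changes taken from the earlier study apply here. The size of the problem for fNIRS, and the power of the fNIRS contrast, cannot be calculated from this document. This should be settled before the data are analysed.

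**What to change.** In section 7, and in line with it in section 9:

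1. For each fNIRS endpoint, state that any acupuncture effect rests on the randomised contrast in the scanned subset: week-8 value modelled on arm and baseline value (ANCOVA), reported as the adjusted difference with 95% CI. Keep the comparisons of rest, 0-back and 2-back as a description of task response.
2. Report within-arm changes, clinical and fNIRS, descriptively as mean change with CI, with no efficacy claim attached.
3. Use the Wilcoxon signed-rank test for any non-normal paired comparison that is kept, and confine Mann–Whitney U to comparisons between arms.

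The contrast in item 1 is fully randomised only if the choice of patients for scanning does not depend on their allocation. The article does not say how they are chosen, so one sentence on this belongs with the change.

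The cost is analysis wording only: no new visits, scans or patients. The downside is that between-arm fNIRS estimates will look less impressive than before–after p-values.
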